### Participants

Participants will be recruited from rheumatological outpatient clinics in the capital region of Copenhagen. Participants in this study are all patients followed by the participating rheumatologic departments. The participant must have moderate to high disease activity, and it must have been decided by the individual departments (at a conference between rheumatologists), that the patient should start or switch biologic treatment.

The patient is invited to participate in the study by a physician in the rheumatological outpatient clinic during a routine visit. Oral and written information will be provided. If the patient agrees to participate, an informed consent form is signed. A screening visit is performed to ensure that the patient meets the criteria for participation.

Inclusion criteria for both groups (axSpA and PsA) are age $$ \ge $$ 18 years at the time of consent, a clinical indication for a biological drug as assessed by the treating physician, sufficient contraception for women in addition to the ability and willingness to provide written informed consent and compliance with the requirements of the study protocol.

For patients with axSpA additional inclusion criteria are a diagnosis of axSpA according to the Assessment of SpondyloArthritis International Society (ASAS) classification criteria [27, 28], active inflammation on MRI of the SIJs and/or spine [29] as evaluated by a central SpA imaging expert and/or radiographic modified New York criteria [30] fulfilled, and total back pain as measured on a VAS scale ≥40 mm (0–100 mm) at baseline.

For patients with PsA additional inclusion criteria are PsA according to Classification Criteria for Psoriatic Arthritis (CASPAR) [31], negative rheumatoid factor (RF) and anti-cyclic citrullinated peptide (anti-CCP), and ≥ 1 tender and swollen joint in addition to two further anatomical localizations with clinical signs of inflammation (i.e., tender enthesis and/or tender and/or swollen joint) assessed at screening and baseline. For patients to fulfill the axial PsA component they must have imaging documented axial involvement on MRI, radiography, or low-dose CT as judged by a central SpA imaging expert.

Exclusion criteria includes contraindications to ixekizumab (serious hypersensitivity to the active substance or the excipients, clinically important active infections (e.g., active tuberculosis), and administration of live vaccines during treatment with ixekizumab) or to MRI (such as metal implants, pregnancy, pacemaker or other implants or electronic devices incompatible with MRI); prior exposure to ixekizumab or other biologic agents targeting IL-17 or the IL-17 receptor; treatment with more than one prior TNF inhibitor; and prior use of bDMARDs other than TNF inhibitors. Patients with active inflammatory bowel disease are also excluded. Use of any investigational drug or device within one month prior to randomization, or within five half-lives of the investigational product (whichever is longer), is not permitted. Additionally, any use of oral, intravenous, intra-articular, or intramuscular corticosteroids within one month prior to the baseline MRI is grounds for exclusion. DMARDs are permitted during the study, provided the dose remained stable for at least one month prior to the first MRI. Further exclusion criteria includes pregnancy or lactation; known recent drug or alcohol abuse; diagnosis of a severe psychiatric disorder; inability to comply with study procedures due to physical or mental limitations; and inability to speak, read, or understand Danish.

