### Assessments

During the 2-year study period, patients will have eight visits to the outpatient clinic, three of which are major assessment visits (months 4, 12, and 24) (see Fig. 1, dark blue arrows). At the major assessment visits, treatment efficacy, and disease activity are evaluated. Patients with ASDAS low disease activity (ASDAS ≤2.1) (axSpA) or DAPSA low disease activity (DAPSA ≤14) (PsA) continue treatment with sc. inj. ixekizumab 80 mg every 4 weeks. Patients, who are not responding (defined as having ASDAS > 2.1 or DAPSA > 14), change treatment at the discretion of the treating rheumatologist and according to the available guidelines from the Medicine Council, Danish Regions (Medicinrådet, Danske Regioner), and they continue to be followed in the study.

All protocol-related assessments will be entered into an electronic case report dedicated to the DAPHNE study.

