### Statistical analysis

The primary analysis will be the intention-to-treat (ITT) population, which comprises all included patients. An additional Per Protocol (PP) analysis will be done as a robustness analysis. The entire patient population will be analyzed for the primary and secondary endpoints. Furthermore, patients will be stratified based on their diagnosis and WB-MRI remission status (remission versus non-remission). Additionally, patients will be stratified as clinical responders versus non-responders at months 4, 12, and 24, based on the presence/absence of ASDAS low disease activity (≤2.1) for patients with axSpA and DAPSA low disease activity (≤14) for patients with PsA. The total inflammatory burden in the entire body, including both peripheral and axial joints and entheses will be assessed at multiple time points - month 0 (baseline), month 4, month 12 (the primary endpoint), and month 24. The total inflammatory burden in the entire body and the WB-MRI remission status will be determined using the sum score of WB-MRI scoring methods for peripheral (WIPE) and axial (CANDEN spine and SPARCC SIJ) inflammation. Further, patients (both the entire patient population and sub-groups stratified by diagnosis, WB-MRI remission and clinical responsiveness) will be evaluated separately for peripheral enthesitis and joint inflammation (using WIPE), and axial inflammation (using CANDEN spine and SPARCC SIJ).

The statistical analyses will include descriptive statistics for all patients (number, median/mean/range of conventional and experimental data), comparisons between groups and within groups (axSpA vs. PsA, WB-MRI remission vs. WB-MRI non-remission, and clinical responders vs. clinical non-responders).

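### Response is a low-activity state with no baseline condition, and the checkable entry criteria do not ensure that patients start above its cut-offs

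*Protocol article*

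**What the plan says.** **Entry (Participants).** A general sentence reads "The participant must have moderate to high disease activity". The same paragraph requires that rheumatologists in conference have decided to start or switch a biologic. The inclusion criteria common to both groups include "a clinical indication for a biological drug as assessed by the treating physician".

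Beyond classification and imaging, the activity thresholds that can be checked are:
- axSpA: "total back pain as measured on a VAS scale ≥40 mm (0–100 mm) at baseline".
- PsA: at least one "tender and swollen joint in addition to two further anatomical localizations with clinical signs of inflammation", and the bracket explaining those signs runs "i.e., tender enthesis and/or tender and/or swollen joint) assessed at screening and baseline".

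No minimum ASDAS or DAPSA is listed.

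**Response (Assessments).** At months 4, 12 and 24, patients who are not responding are "defined as having ASDAS > 2.1 or DAPSA > 14". The section names the complementary states, ASDAS ≤2.1 and DAPSA ≤14, low disease activity.

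**Analysis (Statistical analysis).** The plan says that "patients will be stratified as clinical responders versus non-responders at months 4, 12, and 24", according to whether that low-activity state is present at the visit. It requires neither a change from baseline nor a month 0 value above the cut-off. The Sample size calculation section lists clinical responders versus non-responders among three planned sub-groupings of the primary endpoint.

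**Data (Tables 1 and 2).** DAPSA is built from joint counts, patient global, pain and CRP, so entheses are not a component. ASDAS and DAPSA are both collected at screening and at month 0.

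**The concern.** The plan calls a state a response. That is harmless if every patient starts outside the state, because reaching it then implies a change. The entry criteria do not secure this. The one sentence that points that way is not tied to the indices used later, and the criteria that are tied to measurements are compatible with low-activity values at month 0.

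The consequence falls on the responder strata. A PsA patient with DAPSA 12 at month 0 and 13 at month 4 would be classed as a responder, although the index rose. If such patients enrol, the responder stratum mixes those who moved into the state with those who were never above the line. The comparison of WB-MRI change between the strata then no longer answers whether clinical improvement goes with imaging improvement. If response is used as an outcome in the planned logistic regression, low baseline activity would partly predict it by construction.

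**Working it through.** The plan gives no baseline distribution of ASDAS or DAPSA and no expected responder rate, so it has no figure of its own to reproduce on this point. The check asks whether a patient who just meets the measurable criteria can lie at or below the responder cut-offs.

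**Inputs from the document:** back pain ≥40 mm; one tender and swollen joint plus two further sites, for which tender entheses suffice; cut-offs 2.1 and 14; the components of each index (Table 1).

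**Assumed inputs:** the standard index formulas, which the article does not print, and the item values used below.

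- ASDAS-CRP = 0.12 × back pain + 0.06 × morning stiffness + 0.11 × patient global + 0.07 × peripheral pain + 0.58 × ln(CRP in mg/L + 1), with VAS items in cm.
- DAPSA = tender joints + swollen joints + patient global (0–10) + pain (0–10) + CRP in mg/dL.

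**axSpA at the entry minimum (back pain 40 mm)**

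All four VAS items at 40 mm: (0.12 + 0.06 + 0.11 + 0.07) × 4 = 0.36 × 4 = 1.44.

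| CRP (mg/L) | 0.58 × ln(CRP + 1) | ASDAS | ≤2.1? |
|---|---|---|---|
| 2 | 0.64 | 2.08 | yes |
| 3 | 0.80 | 2.24 | no |
| 5 | 1.04 | 2.48 | no |

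The highest CRP that keeps ASDAS at or below 2.1 is exp[(2.1 − VAS part)/0.58] − 1:
- other three items at 40 mm: exp[(2.1 − 1.44)/0.58] − 1 ≈ 2.1 mg/L
- other three at 20 mm: VAS part 0.48 + 0.24 × 2 = 0.96, giving about 6.1 mg/L
- other three at 0: VAS part 0.48, giving about 15 mg/L

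**PsA (CRP 0.5 mg/dL throughout)**

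| Tender / swollen joints | Global, pain | DAPSA | ≤14? |
|---|---|---|---|
| 1 / 1, plus two tender entheses | 5, 5 | 1 + 1 + 5 + 5 + 0.5 = 12.5 | yes |
| 3 / 1 | 4.5, 4.5 | 3 + 1 + 4.5 + 4.5 + 0.5 = 13.5 | yes |
| 3 / 1 | 5, 5 | 3 + 1 + 5 + 5 + 0.5 = 14.5 | no |
| 3 / 3 | 3, 3 | 3 + 3 + 3 + 3 + 0.5 = 12.5 | yes |
| 3 / 3 | 4, 4 | 3 + 3 + 4 + 4 + 0.5 = 14.5 | no |

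With one tender and one swollen joint, DAPSA is ≤14 whenever global + pain + CRP ≤12. The gap is clearest here, because the two tender entheses count for entry and add nothing to the index.

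**Reading.** The measurable criteria are compatible with values on both sides of each cut-off. They neither force nor exclude a low-activity index at month 0. The share of such patients does not follow from anything in the document.

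**The case against.** The strongest reply is that the article already excludes these patients. It requires moderate or high activity, a conference decision on biologic treatment and a physician's indication, and it labels ASDAS ≤2.1 and DAPSA ≤14 as low activity. Read together, a patient with DAPSA 12 is not meant to enrol. As a statement of intent this stands. It does not settle the analysis, because the activity sentence names no index, cut-off or visit, and the other two requirements rest on judgement. None of them ensures that a patient later called a responder was above the line at month 0.

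A second reply is that an article may leave the operational definition, and the handling of baseline status, to the full protocol or the SAP. That would excuse silence. On response, however, the article states a rule that depends only on the state at the visit.

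A third is that reaching low disease activity is a legitimate target, openly stated. This is true. The difficulty is using it to separate responders from non-responders when some patients may start there.

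Three stronger readings are tempting, and the documents support none of them:
- **That some patients will be counted this way, or that a given number will.** They could be. With no baseline distribution, any percentage is invented, and the worked axSpA example passes the cut-off once CRP is 3 rather than 2 mg/L.
- **That these patients have little inflammation to lose.** The article's rationale is that clinical assessment captures enthesitis poorly, so a low DAPSA need not mean a low WB-MRI score.
- **That an index minimum should be added to entry.** This is a clinical rule for the sponsor. It is also a trade-off, because DAPSA omits entheses and a threshold on it could turn away enthesitis-dominant PsA, while peripheral enthesitis is the first key secondary endpoint.

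**Conclusion.** The concern holds as a possibility that the plan leaves open, and it is limited to the responder strata. Under the assumed standard formulas, patients who meet the measurable entry criteria can have ASDAS 2.08 or DAPSA 12.5 at month 0, and the stated rule would class them as responders if they stayed there. The number affected is unknown.

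The whole-population primary endpoint (change in WB-MRI total inflammation at month 12) and its sample size do not depend on responder status and are unaffected. No responder rate appears among the endpoints in Table 3. What is exposed is a planned sub-group analysis of the primary endpoint, the accompanying within- and between-group tests, and any regression that takes response as its outcome; the article does not name the outcome of its logistic models. The point merits correction because the remedy is cheap, and not because the main result is at risk.

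**What to change.** 1. Reconcile Participants, Assessments and Statistical analysis on what the activity requirement means: which index, which cut-off and which visit, or a statement that it is a clinical judgement not tied to ASDAS or DAPSA. No entry threshold is proposed here.
2. In Statistical analysis, restrict the responder versus non-responder comparisons, and any regression with response as outcome, to patients with ASDAS >2.1 (axSpA) or DAPSA >14 (PsA) at month 0. Report those already at or below the cut-off as a separate group, with their number by diagnosis.
3. Keep the stratification of all patients as a sensitivity analysis.

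Cost: a few sentences in the protocol or SAP and a somewhat smaller responder analysis set. Both indices are already collected at month 0, so no new data are needed, and patient care does not change.

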### Assessments

During the 2-year study period, patients will have eight visits to the outpatient clinic, three of which are major assessment visits (months 4, 12, and 24) (see Fig. 1, dark blue arrows). At the major assessment visits, treatment efficacy, and disease activity are evaluated. Patients with ASDAS low disease activity (ASDAS ≤2.1) (axSpA) or DAPSA low disease activity (DAPSA ≤14) (PsA) continue treatment with sc. inj. ixekizumab 80 mg every 4 weeks. Patients, who are not responding (defined as having ASDAS > 2.1 or DAPSA > 14), change treatment at the discretion of the treating rheumatologist and according to the available guidelines from the Medicine Council, Danish Regions (Medicinrådet, Danske Regioner), and they continue to be followed in the study.

All protocol-related assessments will be entered into an electronic case report dedicated to the DAPHNE study.

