In this study, we aim to address the abovementioned gaps by conducting a longitudinal investigation of the effects of ixekizumab on peripheral and axial inflammation and structural damage in patients with axSpA and PsA. Through comprehensive assessment using advanced imaging techniques such as WB-MRI and detailed MRI evaluation of the spine, including sCT, and low-dose CT, we seek to provide valuable information on the therapeutic effectiveness of ixekizumab across different disease domains. The primary objective is to assess the effect of ixekizumab on the total inflammatory burden in the entire body (peripheral and axial joints and entheses) of patients with axSpA and PsA, as assessed by WB-MRI.

Here we report the design of the DAPHNE study.

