#### Magnetic resonance imaging (MRI)

Whole-body MRI, including conventional MRI (T1 weighted and STIR sequences) and an MRI sequence used for synthetic CT reconstruction (3D gradient echo sequences), will be performed on all patients at baseline, month 4, month 12, and month 24.

WB-MRI will be performed with patients in a supine position and for the following areas: 1. coronal images of shoulders and anterior chest wall; 2. sagittal images of the cervical, thoracic, and lumbar spine; 3. coronal images of the pelvis and hips; 4. coronal images of hands (positioned under the buttocks); 5. sagittal images of knees; 6. sagittal images of ankles; and 7. axial images of the ankles/feet. 3 mm slice thickness (ST) will be used for hand, wrist, and forefeet (in-plane resolution 0.6x0.6 mm), 4 mm ST for spine and SIJ, and 5 mm ST for anterior chest wall, shoulders, pelvis, knee, and ankles (in-plane resolution 0.5x0.5 mm).

The MRI scans will be performed on a 3 Tesla MRI unit.

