### Endpoints

#### Primary endpoint

The primary endpoint is the change from baseline to month 12 in the total inflammatory burden in the entire body (peripheral and axial joints and entheses), as assessed by WB-MRI, in patients with axSpA and PsA treated with ixekizumab.

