**Key secondary endpoints**	
1.	Change from baseline to *months 12 and 24* in *peripheral enthesitis*, as assessed by WB-MRI, in patients with axSpA and PsA treated with ixekizumab.
2.	Change from baseline to *months 12 and 24* in *peripheral joint inflammation*, as assessed by WB-MRI, in patients with axSpA and PsA treated with ixekizumab.
3.	Change from baseline to *month 24* in *total inflammatory burden in the entire body* (peripheral and axial joints and entheses), as assessed by WB-MRI, in patients with axSpA and PsA treated with ixekizumab.
4.	Description of *patterns of structural damage in sacroiliac joints and spine* in patients with axSpA and PsA by conventional MRI methods, MRI-based synthetic CT, low-dose CT, and radiography.
5.	Description of *changes in structural damage in sacroiliac joints and spine* in patients with axSpA and PsA by conventional MRI methods, MRI-based synthetic CT, low-dose CT, and radiography, during 2 years of therapy with ixekizumab.

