**Other secondary endpoints**	
1.	Change from baseline to *months 4, 12, and 24* in *axial inflammation*, as assessed by MRI, in patients with axSpA and PsA treated with ixekizumab, including separately in the posterolateral elements of the spine (facet joints, costovertebral joints, transverse processes, spinous processes, and perientheseal soft tissues) and in the vertebral bodies.
2.	Change from baseline to *months 4 and 24* in *peripheral enthesitis*, as assessed by WB-MRI, in patients with axSpA and PsA treated with ixekizumab.
3.	Change from baseline to *months 4 and 24* in *peripheral joint inflammation*, as assessed by WB-MRI, in patients with axSpA and PsA treated with ixekizumab.
4.	Change from baseline to *month 4* in *total inflammatory burden in the entire body* (peripheral and axial joints and entheses), as assessed by WB-MRI, in patients with axSpA and PsA treated with ixekizumab.
5.	*Description of differences between axSpA and PsA* inflammatory disease manifestations and their response to ixekizumab therapy at months 4, 12, and 24 (by sacroiliac joint and spine MRI and by WB-MRI).
6.	*Development of improved MRI and CT assessment methods* for axial structural damage assessment.
7.	Description of the *relationship between clinical, patient-reported, and imaging findings* at baseline and during ixekizumab therapy.

*WB-MRI* Whole body magnetic resonance imaging, *axSpA* axial spondyloarthritis, *PsA* Psoriatic arthritis, *CT* computed tomography

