### Statistics

#### Sample size calculation

The primary hypothesis of this study is that ixekizumab will reduce the total inflammatory burden in the entire body of patients with axSpA and PsA, as assessed by WB-MRI. All patients in this study will be treated with ixekizumab and the primary endpoint relates to identifying changes within groups. A guiding sample size calculation was done.

A previous investigator-initiated study with 53 axSpA patients treated with a bDMARD (golimumab) using WB-MRI as an outcome measure showed that the mean change in MRI-total inflammation (MRI axial inflammation + MRI peripheral inflammation (joints and entheses)) at week 52 was 24.8 (*p* < 0.001) with a standard error of 3.6 [55].

The change in WB-MRI total inflammation is the primary endpoint in the current study. If the expected mean of the paired differences is 24.8 and the expected standard deviation is 26.2 (corresponding to a standard error of 3.6) the study would require a sample size of 12 (numbers of pairs) to achieve a power of 0.80 and a level of significance of 0.05 (two-sided).

With an expected drop-out rate of 20% at month 12 the required sample size would be 14 patients.

It is planned to include 65 patients (≥25 with each diagnosis).

Sub-group analyses in regard to the primary endpoints for all groups (axSpA vs. PsA, WB-MRI remission vs. WB-MRI non-remission and clinical responders vs. clinical non-responders) are planned. For this matter, the calculated sample size is considered appropriate to detect a statistically significant change in the total inflammatory burden in the entire body as assessed by WB-MRI at month 12 in both the overall study population and in the individual sub-groups during treatment with ixekizumab.

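### The month-12 and month-24 ITT changes estimate an ixekizumab-first strategy with switching, but the protocol labels them the effect of, or change during, ixekizumab therapy

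*Protocol article*

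**What the plan says.** The switch rule is in the Assessments section. At the major visits (months 4, 12 and 24), patients in low disease activity (ASDAS ≤ 2.1 for axSpA, DAPSA ≤ 14 for PsA) continue ixekizumab. The others "change treatment at the discretion of the treating rheumatologist and according to the available guidelines", "and they continue to be followed in the study".

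Whole-body MRI "will be performed on all patients at baseline, month 4, month 12, and month 24". The Statistical analysis section makes ITT, defined as every included patient, the primary analysis, and adds a per-protocol analysis for robustness.

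Three places attach the result to the drug:

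- Introduction: "The primary objective is to assess the effect of ixekizumab on the total inflammatory burden in the entire body".
- Table 3, key secondary endpoint 5: structural change is described "during 2 years of therapy with ixekizumab".
- Sample size calculation: the sample is called adequate to detect a month-12 change "in both the overall study population and in the individual sub-groups during treatment with ixekizumab". The sub-groups listed there include clinical non-responders.

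The Study interventions section says that ixekizumab is given every 4 weeks for the whole study and forbids other potentially disease-modifying drugs apart from csDMARDs. It does not mention the switch rule.

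The month-4 change in total burden is already an endpoint, listed fourth among the other secondary endpoints in Table 3.

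**The concern.** With no comparator, attribution to ixekizumab depends on what patients were taking when the change occurred. A month-12 mean over all included patients contains some who may have left ixekizumab after month 4. Followed as written, the plan would allow a report that ixekizumab reduced total inflammation by a stated amount, when part of that amount may belong to the next drug. The month-24 key secondary results have a second switch point, at month 12.

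The sub-group claim is affected most directly. Clinical non-responders are the patients whom the protocol tells to change treatment, so a later reduction in that group cannot be described as occurring on ixekizumab for those who switched.

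Study interventions and Assessments also conflict: one has every patient on ixekizumab throughout with other disease-modifying drugs barred, while the other directs some of them to different treatment within the study.

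**Working it through.** **The plan's own figure.** Inputs from Sample size calculation: mean paired change 24.8, SD 26.2, two-sided alpha 0.05, power 0.80. The SD follows from the stated standard error: 3.6 × √53 = 26.2. The exact paired t-test gives power 0.807 at 11 pairs and 0.847 at 12, so the stated 12 is reproduced within one patient. With 20% drop-out from 65, 52 remain and power exceeds 0.999. Power is not the issue.

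**Possible time off ixekizumab, from the visit schedule.** These are ceilings, because they assume that changing treatment means stopping ixekizumab at once:

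- Switch at month 4, seen at month 12: (12 − 4)/12 = 67%.
- Switch at month 4, seen at month 24: (24 − 4)/24 = 83%.
- Switch at month 12, seen at month 24: (24 − 12)/24 = 50%.

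**Effect on the estimate.** Let p be the share of analysed patients who switched at month 4, a their mean month-12 improvement had they stayed on ixekizumab, and b their mean improvement after switching. The ITT mean differs from the stay-on-ixekizumab mean by p × (b − a). The document gives none of p, a or b, so neither the size nor the sign is known. What can be computed is how large b − a must be to matter, for assumed values of p.

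- Standard error with 52 completers: 26.2/√52 = 3.63. A shift of one standard error needs b − a = 3.63/p.
- Overstatement that would remove significance: 24.8 − 2.0076 × 3.633 = 17.5. Per switcher this is 17.5/p.

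| Assumed p (month 4) | Patient-time off drug to month 12, at most (p × 8/12) | Same to month 24 (p × 20/24) | b − a for a one-SE shift | b − a to lose significance |
|---|---|---|---|---|
| 20% | 13.3% | 16.7% | 18.2 | 87.5 |
| 30% | 20.0% | 25.0% | 12.1 | 58.4 |
| 50% | 33.3% | 41.7% | 7.3 | 35.0 |

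The month-24 column ignores further switching at month 12. Every value in the last column exceeds the whole planned change of 24.8. It would fall to 24.8 only at 17.5/24.8 = 71% switching.

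**Sub-groups.** Up to the month-12 scan, only month-4 responders are on ixekizumab by rule. Grouping by month-12 status mixes treatments in both groups:

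- Month-12 responders can include month-4 non-responders who reached low disease activity on the next drug.
- Month-12 non-responders can include month-4 responders who are still on ixekizumab.

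**The case against.** The strongest reply is that ITT with continued follow-up after switching is legitimate, that a per-protocol analysis is already planned, and that handling of post-switch scans belongs in the analysis plan, which is not shown. Much of this stands. ITT should stay. A reader might infer that no on-treatment analysis exists, and that is not so: the per-protocol analysis may well exclude switchers, although the article does not define its set. Its definition is an analysis-plan matter and its absence here is no fault. The month-4 change and the month-4 responder strata are also already planned. None of this changes the stated objective, the 2-year wording or the sub-group claim, which conflict with the switch rule within this document.

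Two further readings are tempting and should not be used:

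- The primary endpoint's phrase "in patients with axSpA and PsA treated with ixekizumab" might be read as a causal claim. It describes the population, all of whom start ixekizumab, and can stand.
- The Discussion's argument that blinded reading makes a control group unnecessary might be cited as further evidence. It is a separate question: a control group would not by itself remove switching, and without one even the month-4 change includes natural course and regression to the mean.

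It is also fair that the switch rates above are assumed, that every off-drug figure is a ceiling, and that discretion may mean few patients stop ixekizumab.

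**Conclusion.** The point holds as a mismatch between what is estimated and what is claimed. The month-12 and month-24 ITT changes estimate an ixekizumab-first strategy with guideline-based switching. They do not estimate the effect of ixekizumab alone or change over two years on it, and the sub-group claim fails for clinical non-responders who have switched. Study interventions also contradicts Assessments.

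A reader might go further and infer that the month-12 result is inflated, or that the primary test is unsafe. The documents support neither. The direction and size of any distortion cannot be derived from them. At 20% to 50% switching, losing significance would need a per-switcher overstatement of 35 units or more, against a planned change of 24.8. These figures rest on the planned mean and SD, 52 completers, and assumed switch rates.

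That post-switch scans enter the ITT analysis is an inference, from ITT on all included patients, continued follow-up and MRI in all; the article does not say so outright.

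**What to change.** 1. Keep ITT on all included patients as primary, and state that the month-12 and month-24 results estimate an ixekizumab-first strategy with switching for inadequate response.
2. Align with this the primary objective in the Introduction, key secondary endpoint 5 in Table 3, and the Sample size calculation. In the last, drop the claim of change on ixekizumab treatment for clinical non-responders.
3. Reconcile Study interventions with the switch rule: limit continuous dosing and the ban on other disease-modifying drugs to patients still on ixekizumab.
4. Report the planned month-4 change in all patients beside the month-12 result, as the estimate on ixekizumab. This assumes that the scan precedes any change made at that visit. Month 4 also falls before csDMARD and NSAID doses are freed and glucocorticoid injections are allowed again.
5. Use the planned per-protocol analysis as the supportive on-ixekizumab analysis by excluding post-switch scans, and note that it selects on response. Carrying each switcher's last pre-switch scan forward is not advised, because it mixes 4-month and 12-month changes.
6. Report the month-12 and month-24 responder groups by whether patients are still on ixekizumab.

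The cost is a narrower headline claim and slightly more analysis work. No scans or patients are added.
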